##### Lifestyle

Data on lifestyle factors related to oral health, such as eating, smoking, and sleep habits, will be collected. At baseline, selected items from the Diet Quality Questionnaire (DQQ) [41] will also be administered to assess the intake of food items associated with an increased risk of periodontal disease. The DQQ consists of yes/no questions regarding the consumption of sentinel foods from 29 food groups consumed on the previous day. For this study, 16 food groups considered highly relevant to the development or prevention of periodontal disease have been selected, including (1) starchy staple foods, (2) vegetables, (3) fruits, (4) sweet foods, and (5) beverages.

To assess participants’ physical activity over the past 7 days, which has been shown to have a significant relationship with periodontal disease, the International Physical Activity Questionnaire short form (IPAQ-SF) [42] is included in the baseline survey. The IPAQ-SF comprises seven items covering four categories: vigorous-intensity activity, moderate-intensity activity, walking, and sitting. It also includes questions on the frequency and duration of physical activity. In the vigorous-intensity category, participants will be asked: “During the last 7 days, on how many days did you do vigorous physical activities like heavy lifting, digging, aerobics, running or fast bicycling?” and “How much time did you usually spend doing vigorous physical activities on one of those days?” Similar questions are asked about moderate-intensity physical activity (e.g., carrying light loads, jogging or bicycling), as well as for walking and sedentary behavior.

##### Delivery method

Information on the mode of delivery (e.g., vaginal delivery or caesarean section) and the associated decision-making process will be asked in the endline survey.

#### Dental checkups

Dental checkups (approximately 10 min per participant) will be conducted at both baseline and endline to collect dental data and diagnose periodontal disease [43]. A full-mouth examination will be performed to assess overall oral hygiene status, evaluating the condition of the teeth (sound, carious, treated, or missing), bleeding on probing (BOP), probing pocket depth (PPD), clinical attachment loss (CAL), plaque, calculus, tooth mobility, and oral dryness. BOP is defined as the presence or absence of bleeding during examination of the periodontal pocket. PPD refers to the distance from the gingival margin to the bottom of the pocket, while CAL is the distance from the cemento-enamel junction to the bottom of the pocket [44–46]. Oral dryness will be assessed using a classification scale based on the condition of the tongue mucosa, with higher grades indicating more severe dryness [47].

##### Diagnosis of periodontal disease

BOP, PPD, and CAL will be measured at six points on each tooth and used to diagnose periodontal diseases, including gingivitis and periodontitis. Gingivitis is diagnosed when BOP is present at 10% or more of the total number of periodontal sites examined. Periodontitis will be diagnosed if either of the following criteria is met: (1) interdental CAL is observed at ≥ 2 non-adjacent teeth, or (2) a buccal or palatal/lingual site exhibits a CAL of ≥ 3 mm and PPD of ≥ 4 mm at ≥ 2 teeth [45, 46].

Participants diagnosed with periodontal disease will be randomized into either the intervention group A or control group B. Participants without periodontal disease will be allocated to control group C.

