Epidemiological studies have proposed both direct and indirect pathways through which periodontal disease may contribute to adverse birth outcomes [19–21]. In the direct pathway, periodontal pathogens can reach fetal-placental tissues via hematogenous dissemination, triggering local inflammation and tissue damage that lead to pregnancy complications. In the indirect pathway, inflammatory cytokines and mediators from the gingiva and/or acute-phase reactants from the liver accumulate in the intrauterine compartment, exacerbating inflammation and contributing to pregnancy complications [20, 22]. The adverse impact of periodontal disease on pregnancy outcomes tends to worsen as the severity of maternal periodontal inflammation increases [23, 24].

Both MNCH and oral health require urgent public health attention in Bangladesh. In 2020, Bangladesh had the highest rate of PTB in South Asia at 16.2% [25]. The prevalence of LBW has remained persistently high at 25.7% in 2000, 24.5% in 2010, and 23.0% in 2020 [26]. The most recent figure exceeds that of many other developing countries [1]. The country’s neonatal mortality rate was reported at 20 deaths per 1000 live births in 2022 [27], which is significantly higher than the SDG target. Data on oral health are scarce, particularly in pregnant women, who are at high risk of developing periodontal diseases. A recent cross-sectional study in Dhaka reported that 95.3% of pregnant women had periodontal disease, with 52.4% diagnosed with gingivitis and 43% with periodontitis [28].

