#### Hypothesis

We hypothesize that integrating an intervention targeting periodontal disease—comprising SRP and CHG mouthwash use—into the MNCH CoC will reduce PTB and LBW, decrease the prevalence of periodontal disease, and improve OHRQoL.

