### Data collection and study outcomes

The primary outcome is PTB (< 37 weeks gestation). Secondary outcomes include LBW (< 2500 g), periodontal disease, and OHRQoL.

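### The periodontal outcome reuses the enrolment diagnosis, one arm of which needs only attachment loss, so the A–B difference is diluted toward no effect

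*Protocol article*

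**What the plan says.** The Hypothesis section expects the intervention to "decrease the prevalence of periodontal disease, and improve OHRQoL". Data collection and study outcomes lists the outcome without a response definition of its own: "Secondary outcomes include LBW (< 2500 g), periodontal disease, and OHRQoL". Dental checkups states that the examinations "will be conducted at both baseline and endline to collect dental data and diagnose periodontal disease".

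The one diagnostic rule is in Diagnosis of periodontal disease, and the same section uses it to decide who is randomised to A or B and who goes to C. It has three parts:

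- Gingivitis: "Gingivitis is diagnosed when BOP is present at 10% or more of the total number of periodontal sites examined".
- Periodontitis, criterion (1): "Periodontitis will be diagnosed if either of the following criteria is met: (1) interdental CAL is observed at" two or more non-adjacent teeth. Nothing else is required.
- Periodontitis, criterion (2): "a buccal or palatal/lingual site exhibits a CAL of" 3 mm or more together with a probing pocket depth (PPD) of 4 mm or more, at two or more teeth.

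Dental checkups adds that "CAL is the distance from the cemento-enamel junction to the bottom of the pocket". Statistical analyses plans a mixed-effects model with a group-by-time interaction for periodontal disease in A v B. Bleeding on probing (BOP) and PPD are recorded at six points per tooth, but no stated outcome is built on them directly.

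**The concern.** An eligibility classification is doing the work of a treatment-response measure. Everyone in A and B is positive at baseline, so the outcome registers success only when a woman loses the label. Under criterion (1) she keeps it for as long as any interdental attachment loss is seen at two non-adjacent teeth. Because no millimetre threshold applies, even a real reduction in clinical attachment loss (CAL) leaves her classified as before. A woman whose bleeding has stopped and whose pockets have closed can therefore be counted as a treatment failure.

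This does not depend on the model. It would be the same in a plain endline comparison of A with B.

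At stake is the interpretation of the trial. The Background describes inflammation as a route from periodontal disease to adverse birth outcomes. Whatever the preterm birth result, readers will ask whether inflammation was controlled in group A, and a label that can outlast the inflammation answers that poorly.

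**Working it through.** **The plan's own figure.** The article gives no calculation for the periodontal outcome. Its only one is for preterm birth: 128 per group for 16.2% v 4.7%. The pooled two-proportion formula, two-sided 5%, 80% power, with continuity correction, gives 127, so the figure reproduces closely; 128/0.8 = 160 per group. I use 128 per arm below as the number with endline data.

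**Maximum share that cannot change.** The Background cites a Dhaka study "with 52.4% diagnosed with gingivitis and 43% with periodontitis". Among women with disease, the periodontitis share is 43/(52.4 + 43) = 43/95.4 = 0.451, or about 0.451 × 160 = 72 women per arm. This is the maximum, reached only if every periodontitis case meets criterion (1) and keeps some interdental CAL.

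**Formulas.** Let f be the fixed share, and rA and rB the assumed resolution rates among women who can revert.

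- Endline prevalence: p = f + (1 − f)(1 − r)
- Difference: pB − pA = (1 − f)(rA − rB)
- Power = Φ[(d − 1.96·SE0)/SE1], where d = pB − pA, SE0 = √[2p̄(1 − p̄)/n], SE1 = √{[pA(1 − pA) + pB(1 − pB)]/n} and n = 128

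**Worked case, f = 0.451, rA = 30%, rB = 10% (assumed).**

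- pA = 0.451 + 0.549 × 0.7 = 0.835; pB = 0.451 + 0.549 × 0.9 = 0.945; difference 0.110.
- SE0 = 0.0391 and SE1 = 0.0385, so power = Φ[(0.110 − 0.0766)/0.0385] ≈ 0.81. About 127 per arm are needed for 80% power.
- If the same rates applied to all women (f = 0): 0.70 v 0.90, difference 0.20, power = Φ[(0.20 − 0.098)/0.0484] ≈ 0.98. About 62 per arm are needed.

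**Range over the unknown share meeting criterion (1), same rates.**

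| Periodontitis cases meeting (1) | Fixed share f | A v B prevalence | Difference, points | Power |
|---|---|---|---|---|
| 100% | 45% | 83.5% v 94.5% | 11.0 | 0.81 |
| 75% | 34% | 80% v 93% | 13.2 | 0.88 |
| 50% | 23% | 77% v 92% | 15.5 | 0.93 |
| 25% | 11% | 73% v 91% | 17.7 | 0.96 |
| 0% | 0% | 70% v 90% | 20.0 | 0.98 |

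**Other assumed rates at the maximum f = 0.451.**

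- 60% v 20%: prevalence 67% v 89%, a 22-point difference instead of 40 and a risk ratio of 0.75 instead of 0.50. Power is still about 0.99.
- 50% v 20%: 16.5 points instead of 30; power 0.92 instead of 0.999.
- 30% v 20%: 5.5 points instead of 10; power 0.25 instead of 0.46.

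**The case against.** A reader might infer that the whole periodontitis diagnosis rests on attachment loss, and that lower prevalence is therefore out of reach for about 45% of randomised women. The article does not support that:

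- Only criterion (1) is attachment loss alone. Criterion (2) also needs PPD of 4 mm or more, so a woman who qualifies only through it can revert when pockets shrink.
- The 45% is not a trial figure. It comes from another study whose case definition is not shown. It assumes the same case mix in a trial that also recruits in Bogura, enrols before 20 weeks and excludes high-risk pregnancies, and it assumes that every periodontitis case meets criterion (1).
- The article does not say that attachment loss persists after treatment. CAL is measured to the bottom of the pocket, so the recorded value can fall; how often it falls to none at enough teeth is not given.
- Large effects remain detectable, as the 67% v 89% case shows. Where power is poor (30% v 20%), it is poor without dilution too.
- The undiluted differences apply one resolution rate to all women, and nothing in the article says that inflammation in women with periodontitis resolves at the same rate as gingivitis.

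It can also be said that prevalence under a referenced case definition is a legitimate outcome, and that reporting of components may sit in the full protocol or analysis plan.

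All of these limits on size stand. The mismatch itself also stands: the article states the hypothesis, the outcome and the definition, and together they make the enrolment diagnosis the endline measure. Randomisation is expected to balance the fixed share between A and B, so no false difference is created, but a real one is reduced whenever that share is above zero.

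**Conclusion.** The point holds as a loss of sensitivity in one secondary outcome. The A–B difference in prevalence is multiplied by (1 − f), where f is at most about 0.45 under the cited case mix and about 0.11 to 0.34 if 25% to 75% of periodontitis cases meet criterion (1). With 30% v 10% resolution, power at 128 per arm falls from about 0.98 to between 0.96 and 0.81.

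This rests on three assumptions that the article does not settle: some interdental attachment loss remains after treatment in women who meet criterion (1), the case mix resembles that of the cited study, and the resolution rates are as assumed above. The outcome is diluted, not unreachable. The preterm birth analysis is unaffected. The change is worth making because it is cheap.

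**What to change.** Keep the present definition for eligibility and for the split between groups B and C. In Data collection and study outcomes and in Statistical analyses, define the maternal periodontal outcome for A v B as:

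- main measure: percentage of sites with BOP at endline;
- supporting measure: percentage of sites with PPD of 4 mm or more at endline;
- each compared between A and B with its own baseline value as a covariate.

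Report the yes/no diagnosis alongside, split into gingivitis and periodontitis, and align the wording of the Hypothesis.

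The cost is a change of wording for one secondary outcome and its analysis, to be made before outcome data are examined. No new measurement is needed, since both quantities come from the planned six-point examinations at baseline and endline. The downside is that the headline result is no longer a simple prevalence.

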#### Antenatal records

Data on birth outcomes, including gestational age at delivery and birth weight, will be extracted from antenatal records. Additional information will also be collected, including maternal height, pre-pregnancy body mass index, blood glucose level, pregnancy complications, and the number of antenatal checkups attended.

### Data management

At each hospital, survey data and antenatal records will be independently entered and electronically stored on password-protected servers, with access restricted to researchers listed in the approved IRB protocol. Dental data will initially be collected using paper-based forms and subsequently entered into electronic databases. All physical forms will be stored in a locked file cabinet in a locked office, accessible only to authorized researchers.

To ensure confidentiality and data security, each participant will be assigned a unique identification number, and all data will be anonymized accordingly. The master file linking participants’ names to their respective ID numbers will be stored in a password-protected folder on a secure computer at the Principal Investigator’s institution. All data analyses will be performed using de-identified data, with no access to personally identifiable information. In the event that a participant withdraws from the study, only the data collected up to the point of withdrawal will be included in the analyses.

Study findings will be disseminated through publications in peer-reviewed scientific journals and presentations at international conferences. The objective is to inform not only medical and academic communities, but also policymakers, in order to facilitate the potential integration of the intervention into institutional and national policies.

### Monitoring

The trial will be monitored on a daily basis by the research team, including the Principal Investigator, research coordinators, and other researchers listed on the IRB protocol. As the procedures involved—dental checkup and treatment—are considered to pose minimal risk to participants, including those with periodontal disease, a formal Data Monitoring Committee will not be established.

Nonetheless, the research team will address any issues that arise during the study to ensure adherence to ethical and regulatory standards. In the event of significant protocol modifications, such as changes to the inclusion/exclusion criteria or alterations to the primary outcome, the Principal Investigator will submit the proposed changes for review and approval by the Research Ethics Committee and the relevant hospital authorities at the study sites.

### Statistical analyses

The primary analysis will follow the intention-to-treat principle, whereby participants will be analyzed according to their assigned groups, regardless of adherence to CHG mouthwash use during pregnancy. Missing data will be handled using multiple imputation procedures available in the MI suite of Stata. To assess the robustness of the findings, sensitivity analyses will be conducted by comparing results from imputed and non-imputed datasets.

Data from the baseline and endline surveys, dental checkups, and antenatal records will be compared across groups to evaluate the effects of the intervention (SRP combined with CHG mouthwash use) on the primary (PTB) and secondary outcomes (LBW, periodontal disease, and OHRQoL). Initial analyses will include descriptive statistics for participants’ socio-demographic and other basic characteristics, followed by bivariate analyses to examine differences in baseline variables between groups A and B, and between groups B and C.

To estimate the causal effect of the intervention on birth outcomes, comparisons will be made between groups A and B. To investigate whether previously reported associations between periodontal disease and adverse birth outcomes hold in our population, groups B and C will be compared.

For multivariable analyses, two types of regression models will be employed. (1) Multiple regression models will be used to evaluate outcomes measured only at endline. (2) Mixed-effect regression models will be applied for outcomes assessed at both baseline and endline, accounting for potential intra-individual serial correlations in the residual.

Specifically, to assess the effectiveness of the intervention on birth outcomes (PTB and LBW), a multiple regression model will be used, with intervention status (group A or B) as the main predictor, adjusting for potential covariates (socio-demographic characteristics, lifestyle, pregnancy-related characteristics, and pregnancy outcomes). For oral health outcomes (periodontal disease and OHRQoL), mixed-effects regression models will be used, including intervention status (group A or B), time point (baseline or endline), and their interaction terms, while adjusting for potential covariates.

To evaluate the association between baseline periodontal disease and birth outcomes in groups B and C, a multiple regression model will be employed, with baseline periodontal status (group B or C) as the exposure, adjusting for potential confounders (socio-demographic characteristics and lifestyle at baseline). To assess change in periodontal status between baseline and endline in groups B and C, another multiple regression model will be used with similar covariate adjustments.

To evaluate the association of baseline periodontal diseases and OHRQoL in groups B and C, mixed-effect regression models will be fitted, including baseline periodontal status (group B or C), time point (baseline or endline), and their interaction term, adjusting for the possible confounding factors listed above.

Statistical significance will be set at a *p*-value of < 0.05. All statistical analyses will be conducted using IBM SPSS Statistics version 26.0 (IBM Corp, Armonk, NY, USA) or Stata version 16.0 (StataCorp LLC, College Station, TX, USA).

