### Sample size calculation

Assuming a baseline PTB rate of 16.2% [25], and expecting the intervention to reduce this to 4.7% [32], a sample size of 128 per group is required to detect this difference with 80% power at a 5% significance level. Accounting for a 20% attrition rate, the total sample size is set at 480 (160 per group).

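### Comparing imputed with non-imputed results cannot reveal bias if the link between preterm birth and missingness differs between groups A and B; a tipping-point analysis should be added

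*Protocol article*

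**What the plan says.** Statistical analyses (protocol article) sets an intention-to-treat primary analysis, with missing data handled by multiple imputation in Stata. For robustness it names a single check: "sensitivity analyses will be conducted by comparing results from imputed and non-imputed datasets". The article describes no departure from missing at random and no tipping-point, pattern-mixture or best/worst-case analysis.

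Other sections bear on how much can be missing, and why:

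- Sample size calculation: "Accounting for a 20% attrition rate, the total sample size is set at 480 (160 per group").
- Antenatal records: "Data on birth outcomes, including gestational age at delivery and birth weight, will be extracted from antenatal records".
- Data management: if a woman withdraws, "only the data collected up to the point of withdrawal will be included in the analyses". A woman who withdraws before delivery then has no birth outcome in the analysis.
- Randomization and blinding: participants are not blinded.
- Basic periodontal treatment and mouthwash use: group A has follow-up cleaning at later antenatal visits; group B gets the same treatment only after the endline checkup.

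**The concern.** A robustness check is useful if it can fail when the assumption behind the primary analysis is false. Here that assumption is that, given what is observed, women with a missing birth outcome have the same PTB risk as comparable women whose outcome is known. Multiple imputation as described assumes this, and so does the analysis of non-imputed data. The two tend to agree whether or not it is true.

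The assumption matters most if the dependence of missingness on PTB differs by arm. Three features of the design make that plausible: participants know their allocation, group A has extra dental contact at antenatal visits, and group B has a reason of its own to stay until endline. If women in A who deliver early are lost more often than those in B, the treatment looks better than it is, and both analyses show the same flattering result.

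The stakes are high because PTB is uncommon and the allowed losses outnumber the expected events.

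**Working it through.** **Inputs.** From Sample size calculation: PTB 16.2% in controls and 4.7% under intervention, 128 evaluable per group, 80% power, 5% significance, 20% attrition, 160 enrolled per group. The efficacy comparison is A against B (Statistical analyses). Sidedness is not stated; two-sided is assumed.

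**1. The plan's own figures.** The continuity-corrected two-proportion formula, two-sided, gives 127 per group against the stated 128, so the figure reproduces closely. The uncorrected formula gives 110. For attrition, 128 / (1 − 0.20) = 160, exactly as stated.

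**2. Losses against events.**
- Allowed losses in A and B: 2 × (160 − 128) = 64 of 320.
- Expected events among the evaluable: 128 × 0.162 = 20.7 in B and 128 × 0.047 = 6.0 in A, together 26.8, or about 27 among 256 women.
- Ratio of losses to events: 64 / 26.8 = 2.4.

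**3. Can the stated check detect the problem?** Simulation with no true effect: 16.2% PTB in both arms, 160 per arm, 20% missing per arm, 2000 replicates, 20 arm-specific imputations each. In B, missingness is unrelated to PTB. In A, the share of PTB cases that go missing is varied.

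| PTB cases missing in A | Complete-case risk difference | Imputed risk difference | False positives (complete-case / imputed) |
|---|---|---|---|
| 20% (unrelated to PTB) | 0.000 | 0.000 | 5.0% / 5.3% |
| 40% | −0.040 | −0.040 | 15% / 15% |
| 60% | −0.082 | −0.082 | 53% / 52% |

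The complete-case bias can be checked by hand. With 40% of PTB cases missing in A, the observed rate is 0.162 × 0.60 / 0.80 = 0.1215, and 0.1215 − 0.162 = −0.0405.

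When 60% of PTB cases are missing in both arms alike, the bias is about zero and false positives are about 5%. Under no effect, the harm comes from the difference between arms.

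**4. Tipping point at the design rates.** Observed: 6/128 in A and 21/128 in B. Pooled z-test p = 0.002; Fisher p = 0.004. Let B's 32 missing women have PTB at about B's rate (5 of 32), so B totals 26/160. Let k of A's 32 missing women have PTB, so A totals (6 + k)/160.

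| k | A total | z-test p | Fisher p |
|---|---|---|---|
| 7 | 13/160 | 0.026 | 0.039 |
| 8 | 14/160 | 0.043 | 0.062 |
| 9 | 15/160 | 0.066 | 0.093 |

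Significance is lost at k = 9 by z-test (9/32 = 28%) and at k = 8 by Fisher (8/32 = 25%). The odds ratios, missing against observed women in A, are (9/23) / (6/122) = 8.0 and (8/24) / (6/122) = 6.8. At k = 9 the full-data difference is 9.4% − 16.3% = −6.9 points. The complete-case result stays at 4.7% − 16.4% = −11.7 points, p = 0.002.

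**5. A smaller observed effect.** Take 10 vs 21 of 128, a risk ratio of 10/21 = 0.48, between the pooled PTB risk ratios of 0.44 and 0.56 cited in the Background. The z-test gives p = 0.035. If the missing women in both arms have B's rate (5 of 32 each), the totals are 15/160 and 26/160, p = 0.066. The odds ratio needed in A is only (5/27) / (10/118) = 2.2. By Fisher, 10 vs 21 is already at p = 0.054, so this example rests on the z-test.

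All these tests are unadjusted stand-ins for the planned covariate-adjusted regression.

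**The case against.** The strongest reply is that the section states nothing false. Comparing imputed with complete-case results is common and legitimate. If the imputation model uses variables outside the analysis model, the comparison can expose sensitivity to missingness that depends on those variables. Further sensitivity analyses may be in a statistical analysis plan that is not shown. This stands in part: that this is the sole check is known only for the article, and the check is worth keeping. But the article itself selects it as the test of robustness, and it does not test the assumption most in doubt.

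The 20% figure is a sample-size allowance, not a forecast of missing gestational ages. Outcomes taken from records may be more complete than the surveys or dental checkups. This stands, and the 64 should be read as what the design tolerates.

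Outcome-dependent missingness that is identical in both arms does not bias a logistic odds ratio. This also stands, and limits the point to dependence that differs by arm.

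A reader might go further and infer three things that the documents do not support:

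- That women who deliver early elsewhere are untraced. The article names antenatal records as the source and does not say whether outside deliveries are followed up.
- That known early pregnancy losses would be given an imputed birth outcome because entry is before 20 weeks. Nothing says that such losses are coded as missing.
- That the check passes whatever the bias. With auxiliary variables the two results could differ somewhat; the defect is that agreement is not evidence against bias that differs by arm.

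**Conclusion.** The point holds in this limited form: the stated comparison cannot reveal bias when the dependence of missingness on PTB differs between A and B, and the attrition the design allows for is large enough for such bias to change the conclusion.

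How readily it would do so depends on the observed effect. At the full design effect the result is fairly sturdy: A's missing women would need roughly 7 to 8 times the odds of PTB seen in A's observed women. At a risk ratio near 0.48, it is enough that they resemble group B.

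These sizes assume 32 missing per arm, two-sided unadjusted tests and 5 PTB among B's missing women. Fewer missing outcomes would make the result harder to overturn. That missingness will differ by arm in this way is a plausible consequence of the design, not something the article states. The plan should be changed, but the primary method need not be.

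**What to change.** Keep multiple imputation as the primary analysis and the non-imputed comparison as a secondary check. Make two additions to Statistical analyses:

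1. A delta-adjusted (tipping-point) analysis of PTB in the same Stata imputation suite. The imputed odds of PTB are multiplied by factors set separately for A and B, over a prespecified grid wide enough to reach the tipping point, for example ×1 to ×10. A grid that stops at ×6 in A with B left at ×1 would miss the design-rate tipping points of 6.8 and 8.0. Report the combinations at which the conclusion changes.
2. The number of missing birth outcomes by arm, so that readers can judge which part of the grid is credible.

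The cost is a few lines of code and one table. Under Trial status, data collection is expected to end in September 2026, so the change can be specified before analysis if made by then.

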### Study sites

This trial will be conducted from April 2025 to September 2026 at two hospitals in Bangladesh: Holy Family Red Crescent Medical College Hospital (HFRC) in Dhaka and TMSS Medical College & Rafatullah Community Hospital (TMSS) in Bogura. Both the obstetrics and gynecology, and dental departments of each hospital will implement the interventions. Research coordinators from Grameen Communications will oversee overall coordination.

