### Study population

Pregnant women attending antenatal checkups will be recruited from the obstetrics and gynecology departments at both hospitals, targeting approximately 225 participants per site. Enrollment will continue until 160 participants are allocated to each study group. Trained healthcare professionals, such as doctors, dentists, nurses, midwives, and dental assistants, who have completed a training program led by the research team, will assess eligibility, explain the study procedures, obtain informed consent, and conduct the intervention.

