### Randomization and blinding

The trial includes three groups: group A (intervention) and groups B and C (control). All participants will first complete a face-to-face interview at the obstetrics and gynecology department following consent. They will then undergo a baseline dental checkup. Participants diagnosed with periodontal disease will be randomized to group A or B using blocked randomization via computer-generated sequence at each site. Those without periodontal disease will be assigned to group C.

Blinding will be maintained for the interviewers and data recorders, who will not be informed of group allocation. However, blinding will not be feasible for the dentists conducting dental checkups or for participants due to the nature of the intervention.

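### Randomisation is blocked by hospital, but hospital is missing from the adjustment sets named for the models; this matters mainly for the non-randomised comparison of groups B and C

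*Protocol article*

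**What the plan says.** Under Randomization and blinding, women with periodontal disease are "randomized to group A or B using blocked randomization via computer-generated sequence at each site". Hospital is thus the only stratification factor that the article states. Group C is not randomised: "Those without periodontal disease will be assigned to group C". Under Study population the recruitment target is set per group and not per group within hospital: "Enrollment will continue until 160 participants are allocated to each study group".

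Statistical analyses then describes the models:

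- **A versus B, birth outcomes.** Here "a multiple regression model will be used, with intervention status (group A or B) as the main predictor, adjusting for potential covariates", and the covariate classes are given as "socio-demographic characteristics, lifestyle, pregnancy-related characteristics, and pregnancy outcomes".
- **A versus B, periodontal disease and oral health-related quality of life.** Mixed models with group, time and their interaction, plus covariates that are not listed.
- **B versus C, birth outcomes.** A regression on baseline periodontal status, "adjusting for potential confounders (socio-demographic characteristics and lifestyle at baseline". The other B-versus-C models refer back to this set or to a similar one.

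Hospital is named in none of these as a covariate, stratum or random effect. The correlation that the mixed models address is within person. The socio-demographic items listed under that subheading do not mention hospital or region. The Discussion treats the two regions only as a limit on generalisability.

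**The concern.** Two principles are in play, and they carry different weight.

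First, an analysis should reflect the way in which patients were randomised. When the sequence is blocked within hospital and the model ignores hospital, the variance that the test assumes still contains the between-hospital component that the design removed.

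Second, in a non-randomised comparison a variable related to both exposure and outcome has to be adjusted for. The B-versus-C comparison serves the first stated aim of the study, which is to see whether the reported association between periodontal disease and adverse birth outcomes holds in this population. Whether a woman falls into B or C depends on how common the disease is where she attends, and on the bleeding, pocket-depth and attachment readings taken in her hospital's dental department. If PTB rates also differ between Dhaka and Bogura, a difference between hospitals can pass for an association with periodontal disease, or can hide one.

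**Working it through.** **The plan's own figure.** For 16.2% versus 4.7%, two-sided 5%, 80% power:

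n = [1.960·√(2·0.1045·0.8955) + 0.8416·√(0.162·0.838 + 0.047·0.953)]² / 0.115² = 109.9, so 110.

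With continuity correction: (109.9/4)·[1 + √(1 + 4/(109.9·0.115))]² = 126.7, so 127. This is within one of the stated 128, and 128/0.80 = 160. The calculation has no site term, so nothing below alters it.

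**A versus B.** Inputs: 128 per arm (Sample size calculation), an equal split between hospitals (assumed), and a gap between hospitals in control PTB centred on 16.2% (assumed). For the power figures, the same risk ratio of 4.7/16.2 is taken at both hospitals.

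Variance used by the unadjusted test: p̄(1 − p̄) = 0.162·0.838 = 0.1358. True variance with balance within hospital, for rates of 10.2% and 22.2%: (0.102·0.898 + 0.222·0.778)/2 = 0.1322. The ratio is 0.973. True type I error = 2·[1 − Φ(1.960·√(0.1358/0.1322))] = 0.047.

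| Assumed gap in control PTB | Type I error, hospital ignored | Power, hospital ignored | Power, hospital in model |
|---|---|---|---|
| 0 points | 0.050 | 85.7% | 85.7% |
| 8 points | 0.049 | 85.8% | 86.0% |
| 12 points | 0.047 | 86.0% | 86.3% |
| 20 points | 0.042 | 86.4% | 87.4% |

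(Power exceeds 80% here because no continuity correction is applied.)

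**B versus C, with no true association.** Inputs: Dhaka prevalence 95.3% (Background, from a cross-sectional study in that city), Bogura prevalence (assumed), equal numbers screened at each hospital (assumed), half of the diseased women going to B, and PTB of 12% at one hospital and 20% at the other (assumed).

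Worked example with Bogura at 60% and 240 screened per hospital:

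- B: 240·0.953/2 = 114 from Dhaka and 240·0.60/2 = 72 from Bogura.
- C: 240·0.047 = 11 from Dhaka and 240·0.40 = 96 from Bogura.
- With PTB 12% in Dhaka and 20% in Bogura: B = (114·0.12 + 72·0.20)/186 = 15.1%; C = (11·0.12 + 96·0.20)/107 = 19.2%.
- OR = (0.151/0.849)/(0.192/0.808) = 0.75. With the two site rates swapped it is 1.38.

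| Bogura prevalence | Dhaka share of B | Dhaka share of C | OR if Dhaka PTB is higher | OR if Bogura PTB is higher |
|---|---|---|---|---|
| 95.3% (equal) | 50% | 50% | 1.00 | 1.00 |
| 90% | 51% | 32% | 1.13 | 0.89 |
| 80% | 54% | 19% | 1.25 | 0.82 |
| 60% | 61% | 11% | 1.38 | 0.75 |
| 40% | 70% | 7% | 1.49 | 0.70 |

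With a 4-point gap the 40% row becomes 1.21 or 0.83. With no gap every entry is 1.00. Centring the 8-point gap on 16.2% in place of 16% gives 1.48 for 1.49. The shares do not depend on the number screened, provided that it is equal at the two hospitals.

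**The case against.** The strongest reply is that this is a condensed article. It names classes of potential covariates and not variables, the socio-demographic list is open-ended, and a statistical analysis plan may well add hospital. Nothing in the text says that hospital will be excluded, so the randomisation and analysis sections do not contradict each other. For the A-versus-B oral-health models this reply stands in full: a reader might infer that hospital is left out of every model, but there the covariates are simply not listed. It stands less well for the A-versus-B birth-outcome models and for B versus C. There the article does name the adjustment sets and passes over its own stratification factor, and treatment centre is not naturally a socio-demographic or lifestyle item.

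A reader might also infer that the primary comparison is biased. It is not, because blocking within hospital keeps the arms balanced by site. Even the gain in precision depends on scale. The 2.7% smaller variance applies to the risk difference. In a logistic model with 128 per arm, rates of 10% and 22% and no effect, adding hospital raises the variance of the log odds ratio from 2/(128·0.16·0.84) = 0.1163 to 1/[32·(0.10·0.90 + 0.22·0.78)] = 0.1195, while a non-null conditional estimate moves outward.

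For B versus C, the objection that the inputs are assumed is fair. The documents give no Bogura prevalence and no PTB rate by hospital, and the 95.3% is not from the trial hospital. The odds ratios are crude, and planned adjustment for education, employment, household assets and lifestyle may remove part of a site difference.

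Finally, one might ask for pre-pregnancy body mass index and maternal height in the B-versus-C models, since both are collected. Nothing in the documents shows that leaving them out matters, so that is not part of this point.

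**Conclusion.** The point holds, chiefly for B versus C. Hospital defines the randomisation strata but is absent from the adjustment sets named for the A-versus-B birth-outcome models and for the B-versus-C models.

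For A versus B the consequence is negligible: no bias, a slightly conservative test, and a power change of under 1 point for assumed site gaps up to 12 points. The reason to include hospital there is consistency with the design.

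For B versus C the consequence could be material. Over the assumed ranges (Bogura prevalence from 40% up to equal with Dhaka, PTB gap of 0 to 8 points, either hospital higher) the crude spurious odds ratio lies between about 0.70 and 1.49. It is exactly 1.00 if either prevalence or PTB rate is the same at both hospitals. It would be wrong to read this range as a demonstrated bias. It shows that hospital can confound the comparison under conditions that the documents neither establish nor rule out.

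**What to change.** State in Statistical analyses that hospital enters as a fixed effect in every A-versus-B and B-versus-C model, for PTB, low birth weight, periodontal disease and oral health-related quality of life. With two hospitals a random effect for site is not workable. The imputation models should carry the same term, so that they match the analyses they feed.

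The cost is one degree of freedom per model and a sentence of text. No new data are needed, since each woman's hospital is known, and the sample size stays at 128 per group before attrition and 160 after. The Trial status section expects data collection to run to September 2026, so the change can be fixed in advance of complete data.
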